#### Aim 3: Pragmatic, Hybrid Implementation Trial (Implement the Connected Care Solution via a Pilot, Pragmatic Trial Comparing Clinical Outcomes Between the Connected Care Model and Standard Practice)

Patients identified as having high risk for pressure injury recurrence will be randomized to either the connected care model (Figure 2) or the standard model of care for a 1-year follow-up time frame. Our implementation outcomes include important stakeholders’ assessment of feasibility, acceptability, appropriateness, costs, and improved monitoring. Our pilot effectiveness outcomes are rate of wound healing for prevalent cases, incidence and recurrence of pressure injuries, early identification of wounds, and hospital admissions or readmissions.

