#### Control Protocol

If participants are randomized into the control group, the standard of care protocol will be followed as used in the seating clinic. Demographic and additional variables will be collected from participants similar to those in the intervention group, and their clinical visit will be recorded for assessment of the visit.

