#### Primary Pilot Clinical Trial Effectiveness Outcomes

The primary effectiveness of the intervention will be captured via the collection of the following clinical outcomes: wound recurrence, early identification of wounds, wound healing, and hospital admission or readmission. The data for these metrics will be abstracted during the full year (365 days) after the study-related clinical visit for both the control and intervention group participants. Then, 2 independent therapist team members will abstract the medical records of each participant to search for the occurrence of an incident wound, stage at which wounds are identified, time frame of wound healing, and occurrence of a hospital admission or readmission directly related to a seating area pressure wound. Comparisons between groups for the primary outcome measures will be made using a 2-tailed *t* test. Additional comparisons will be made with regression and mixed effect models to explore the role of covariates on the study findings.

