#### Potential Limitations and Alternative Strategies

In addition to the potential limitation described for aim 2, aim 3 has the added potential of loss to follow-up. As the long-term follow-up data are passively extracted from the medical record, we acknowledged that patients may seek care outside the original health system they were recruited from. In addition, for participants who have data that we cannot access, we will seek the approval of the participant to access their medical records from other medical systems.

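### Wound healing time comes from passively collected charts and is compared by t test, which treats a bracketed closure date as exact and has no place for wounds still open at day 365

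*Protocol article*

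**What the plan says.** The protocol article's section on primary pilot effectiveness outcomes lists wound healing beside recurrence, early identification and hospital admission. On data collection it says that "2 independent therapist team members will abstract the medical records of each participant", and among the items sought are "stage at which wounds are identified, time frame of wound healing". On the window: "The data for these metrics will be abstracted during the full year (365 days) after the study-related clinical visit". The named comparison for the primary outcomes is a two-tailed t test. Regression and mixed models are added to explore covariates.

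The aim 3 limitations section calls the follow-up passive ("As the long-term follow-up data are passively extracted from the medical record") and accepts that "patients may seek care outside the original health system they were recruited from". For controls, "the standard of care protocol will be followed as used in the seating clinic". No section sets a wound assessment schedule after the study visit for either arm.

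The skin check confirmed at the connected-care telehealth visit and the daily skin log kept during mat use are not named as sources for the healing outcome, and neither covers the year of follow-up.

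The aim 3 summary names the outcome differently, as "rate of wound healing for prevalent cases".

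**The concern.** The data source and the test do not fit each other. Passive records give a closure date only if someone happened to write one down. Otherwise they give two dates with closure somewhere between them, which is an interval-censored time. A wound still open at day 365, or at the last note before a participant moves to another health system, has no healing time at all. A t test needs one exact number per participant. Unhealed wounds must then be dropped, which removes the slowest healers, or be given an arbitrary value.

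Two things are at stake. The sample size section says the pilot will be used to power the full trial, so a healing time carrying a documentation lag would be passed on as if it were true. In addition, if wounds in one arm are documented at wider intervals than in the other, the lag differs by arm and appears as a treatment difference.

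**Working it through.** **Plan's own figure.** There is none to reproduce for healing. The only sizing figure is 26 per arm, from guidance of 25 per arm. This point does not depend on it.

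**Inputs.** From the article: 365 days of follow-up, passive record extraction, two-sided t test at 0.05. Not in the article, so assumed: contact gaps, the true healing distribution, the number of wounds, and the rule that closure is dated at the first closed note.

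**Step 1, lag under that rule.** Recorded time = true time + wait to the next contact. With regular contacts every g days and a random start, the wait is uniform on 0 to g, so its mean is g/2. With irregular (Poisson) contacts of mean gap g, the mean wait is g.

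| Assumed gap | Mean lag, regular | Mean lag, irregular |
|---|---|---|
| 14 days | 7 | 14 |
| 30 days | 15 | 30 |
| 60 days | 30 | 60 |
| 90 days | 45 | 90 |

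**Step 2, effect on a recorded median.** For exponential healing with assumed median 60 days, the rate is λ = ln 2/60 = 0.01155. For regular contacts the recorded median is [ln 2 + ln((e^(λg) − 1)/(λg))]/λ.
- g = 30: λg = 0.3466 and (1.4142 − 1)/0.3466 = 1.195. The median is (0.6931 + 0.1783)/0.01155 = 75 days.
- g = 60: λg = 0.6931 and (2 − 1)/0.6931 = 1.443. The median is (0.6931 + 0.3665)/0.01155 = 92 days.

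**Step 3, effect on the arm comparison.** Simulation with identical true healing in both arms (gamma), regular contacts, 8,000 trials per cell. Rejection rates of the t test are shown for 13 / 26 healing wounds per arm. Twenty-six would mean that every participant has a wound that heals.

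| Gaps in the two arms | Spurious mean difference | Mean 90, SD 60 | Mean 60, SD 40 |
|---|---|---|---|
| 30 v 30 | about 0 days | 5.0% / 4.7% | 4.8% / 4.5% |
| 30 v 60 | 15 days | 9.6% / 14.6% | 14.7% / 24.2% |
| 30 v 90 | 30 days | 22.0% / 40.5% | 39.1% / 67.3% |

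The first row matters as much as the others: with equal spacing the lag cancels and the error rate is nominal. Irregular contacts double the differences.

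**Step 4, wounds without a healing date.** Under the same exponential assumption, the share of wounds present at the visit that are still open at day 365 is 0.5^(365/60) = 1.5% for a median of 60 days and 0.5^(365/90) = 6.0% for 90 days. For a wound arising at, say, day 275, 90 days remain, and with a median of 60 days 0.5^(90/60) = 35% would still be open at the end. The unhealed share therefore depends heavily on whether new wounds count.

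**The case against.** **The article does not state a first-closed-note rule.** It condenses a fuller plan, and it says standard operating procedures will be developed. How closure is defined and dated could properly sit there, so the lag in the working is conditional on a rule supplied for illustration. That stands. However, the passive source and the t test are stated, and a better dating rule does not give a t test a way to use bracketed dates or unhealed wounds. The article's mixed models and multiple imputation address missing values, not interval or right censoring.

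**A reader might infer that the arms will be seen at different frequencies, because one receives a web-based visit and the other usual care with telehealth where suitable.** The article does not support this. Those sections describe the study visit and its preparation, not how often wounds are seen over the following year, and the same abstraction window applies to both arms. Nor do they establish that spacing will be equal.

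**A reader might also conclude that the outcome simply measures visit frequency.** It does not. Recorded time is true healing time plus a lag, so the two are mixed, not interchangeable.

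**The outcome may not be a time at all.** A healing rate for prevalent cases could mean the proportion healed by day 365, for which a lag of some weeks matters much less. That is a fair reading of the aim 3 summary, but the outcomes section asks for a time frame, and the two need to be reconciled.

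**Chart-recorded time may be what the full trial needs.** If that trial also uses chart abstraction, this is partly true. The overstatement matters when the figures are read as true healing times.

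**Conclusion.** The point holds as a mismatch between a stated data source and a stated test. Closure dates are bracketed, some wounds may have no closure date, and the t test handles neither. This needs no assumption about the arms.

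The sizes are conditional. If closure is dated at the first closed note, recorded times run late by about half the gap for regular contacts: 15 or 30 days for assumed gaps of 30 or 60 days. Bias in the arm comparison requires contact spacing to differ by arm, which the article neither states nor excludes. With equal spacing there is no spurious difference. Healing times, contact gaps and wound counts are all assumptions, and the error rates in the working show what could happen, not what will. The weakness is common in chart-based outcomes, but this is a primary outcome and the repair is cheap, so it should be made.

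**What to change.** In the section on primary pilot effectiveness outcomes:

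1. For each wound present at the study visit or arising later, have the two planned abstractors record the first date noted, the last date documented open and the first date documented closed.
2. Replace the t test for healing with a simple interval-censored comparison by arm: one treatment parameter in a Weibull or proportional hazards model, or a nonparametric interval-censored test if wounds are few. Right-censor wounds open at day 365 or at last contact. If a participant can contribute several wounds, allow for the clustering or take one index wound.
3. Reconcile the time frame of healing with the healing rate for prevalent cases in the aim 3 summary. Say which is the outcome and whether new wounds count. For new wounds the clock starts when someone first notes them, and earlier identification is itself an outcome that the intervention is meant to change.
4. Report the number and spacing of wound notes by arm, so that readers can judge whether documentation differed.

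The cost is a few date fields on an abstraction already planned and a standard model in the named software (SAS or R). The drawbacks are a wider interval, limited stability if few participants have wounds, and the remaining assumption that contact timing is not driven by healing. That assumption is doubtful in usual care and should be stated as a limitation.

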#### Telehealth Clinical Visit

During the visit, the therapist will use the standard clinical notes and the data provided on the mHealth report to guide the patient participant through the typical steps of a therapy visit focused on the seating and mobility needs related to pressure injury prevention. The telehealth visit will be completed using the standard Zoom interface. The therapist will use all the information they have available to determine the next steps in the patient’s care plan. The clinic visits will be recorded, so that the study team can provide additional observations for use in process improvement. The therapist will ask for confirmation of a skin check performed on the day of the visit with assistance from a caregiver, if necessary.

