#### Study Design

This single-site randomized controlled trial will use a modified intention-to-treat analysis. Randomization will be a stratified, block randomization with stratification based on wheelchair type (manual vs power) and current wound severity (no wound or stage 1 vs stage 2 or stage 3). The intervention group (26/52, 50%) will receive the connected care model that used AW-Shift in combination with telehealth. The control group (26/52, 50%) will receive the standard of care that uses telehealth when appropriate. The statistician will be masked to the group allocation information for the outcome measure analysis.

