#### General Statistical Methods

All tests are 2 sided, with a 0.05 type-1 error rate. Analysis will be conducted using SAS (SAS Institute) and R software (GNU Project). Mean and SD or median and IQR will be reported for all demographic, predictor, and outcome variables, as appropriate. For all outcome measures, the effect of relevant biological variables including sex, age, level of sensation, and pressure injury history will be assessed as covariates in the analysis. In addition, wheelchair type will be included as a covariate. Variables will be transformed as necessary to meet the appropriate distributional assumptions for modeling (eg, normality). For missing data, mixed models can be used to handle missing data naturally, so that all available data points may be analyzed, irrespective of whether the participant had some outcome data missing. However, analyses of data with multiple imputation for missing data may be attempted if the data are likely to be missing at random.

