#### Sample Size

The sample size for this pilot study (N=52; n=26, 50% per group) is based on guidance that for a trial with 90% power and 2-sided 5% significance, pilot trial sample size of 25 participants per treatment arm is sufficient for an expected small, standardized effect size (0.2) [39]. We do not have the needed data for our primary outcomes to directly determine the power of our planned study design; however, this pilot study will be used to power the full clinical trial. Furthermore, we have used approaches to optimize our statistical power including blocking within the design itself that adjusts for covariates during randomization to reduce imbalance and triangulating the findings of quantitative analyses with qualitative data in mixed methods designs [41].

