#### Potential Risks

There is the potential for skin irritation from sitting on a pressure mat for long periods. Participants may sit on the pressure mat throughout the day or may simply use it for short periods while performing their prescribed activities. Participants will be instructed to do a skin check every day and log their findings.

Participants are instructed to call the study coordinator if a new area of skin breakdown or wound occurs while they are using the pressure mat or if a current wound worsens. The participant will be asked to remove the mat until the skin breakdown or wound resolves. If the area does not resolve and worsens further, the participant will again contact the study coordinator and will then be referred to their typical clinical care provider in the case of a potential, new-onset incidence of pressure ulcers of stage 3 or 4. Initializing and deploying the AW-Shift system will require performing transfers and weight shifts. Transfers always have some risk of injury or fall, and the participant will be advised to transfer in their usual manner. Weight shifts will include typical functional movements, such as leaning forward and sideways, but participants will be instructed to only perform weight shifts with which they are comfortable. Risks from transferring on their own while the sensors are on the wheelchair are no different than transferring without the sensors present.

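### Early identification is compared by t test on wound stage, which exists only for participants who develop a wound, a post-randomization subset that the intervention aims to change

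*Protocol article*

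**What the plan says.** Primary Pilot Clinical Trial Effectiveness Outcomes names four primary outcomes: wound recurrence, early identification, wound healing, and hospital admission or readmission. Two therapists abstract each medical record for the 365 days after the study visit. They look for an incident wound, with no minimum stage given, and for "stage at which wounds are identified, time frame of wound healing". Admissions are limited to those caused by a seating-area wound; incident wounds carry no such limit. Groups are compared on the primary outcomes by a two-tailed t test, and General Statistical Methods adds: "All tests are 2 sided, with a 0.05 type-1 error rate". No stage value is given for a participant without a wound.

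The Aim 3 summary lists the effectiveness outcomes as "rate of wound healing for prevalent cases, incidence and recurrence of pressure injuries, early identification of wounds" together with admissions, so there healing is limited to prevalent cases. The primary outcomes section does not repeat that limit.

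Two passages bear on how wounds are found in the connected-care arm. Potential Risks, on the pressure mat, says: "Participants will be instructed to do a skin check every day and log their findings". Telehealth Clinical Visit says: "The therapist will ask for confirmation of a skin check performed on the day of the visit". Control Protocol says that standard care is followed and describes no skin-check schedule.

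**The concern.** Two separate problems meet in this section.

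The first is conditioning. Stage at identification is observed only after a wound occurs, and the trial expects the intervention to alter who gets one. If mild wounds are prevented, those that remain are on average more severe, and a t test on stage would count that success against the intervention.

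The second is ascertainment. Recurrence can be assessed in every participant, so it is not a subset comparison. But it counts recorded wounds of any stage, and earlier identification is itself a goal. If connected care brings to the record stage 1 areas that would otherwise never be noted, the recurrence count rises without any more injury.

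The pilot is meant to supply the data for powering the full trial. An early-identification estimate that partly reflects who was left to be staged would carry into that design.

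**Working it through.** **Design figures.** "The intervention group (26/52, 50%) will receive the connected care model", so 2 × 26 = 52, as stated. The document has no data for powering its primary outcomes. All wound rates by stage below are therefore assumptions, and only directions should be relied on.

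**Check 1: two scenarios.** For recorded stage proportions p1, p2 and p3 per randomized participant:

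- any wound = p1 + p2 + p3
- mean stage among the wounded = (p1 + 2·p2 + 3·p3) / (p1 + p2 + p3)
- mean score over all randomized, with no wound = 0: p1 + 2·p2 + 3·p3
- stage 2 or higher = p2 + p3

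Scenario A prevents half of stage 1 and a quarter of stage 2. In scenario B more stage 1 is recorded while stage 2 or higher falls.

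| | Control | A | B |
|---|---|---|---|
| p1 / p2 / p3 | 0.20 / 0.20 / 0.10 | 0.10 / 0.15 / 0.10 | 0.35 / 0.17 / 0.08 |
| Any wound | 0.50 | 0.35 | 0.60 |
| Mean stage, wounded only | 0.90/0.50 = 1.80 | 0.70/0.35 = 2.00 | 0.93/0.60 = 1.55 |
| Mean score, all randomized | 0.90 | 0.70 | 0.93 |
| Stage 2 or higher, all randomized | 0.30 | 0.25 | 0.25 |

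In A, recurrence looks better and stage looks worse. In B, recurrence looks worse and stage looks better. An ordinal score over all randomized participants is right in A but wrong in B (0.93 against 0.90). By ranks in B, the chance that an intervention participant is worse is 0.35×0.50 + 0.17×0.70 + 0.08×0.90 = 0.366. The reverse is 0.20×0.40 + 0.20×0.75 + 0.10×0.92 = 0.322. Stage 2 or higher is right in both.

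**Check 2: a model that separates true from recorded wounds.** Assume a true risk of 38% (top of the incidence range in the Background) and 40/40/20% of wounds peaking at stage 1/2/3. A wound is recorded at stage 1 with probability d1 = 0.40, otherwise at stage 2 with probability d2 = 0.80 if it gets that far, otherwise at stage 3.

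| | Any wound recorded | Mean stage |
|---|---|---|
| Control | 27.1% | 1.47 |
| Mild wounds prevented (risk ratios 0.5 / 0.75 / 1) | 20.7% | 1.53 |
| Detection only, d1 = 0.80 | 34.4% | 1.12 |
| True risk cut by 20%, d1 = 0.80 | 27.5% | 1.12 |
| True risk cut by 50%, d1 = 0.80 | 17.2% | 1.12 |

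A true 20% reduction can thus be hidden on recurrence; a 50% reduction is not. Directions are the same at true risks of 50% and 80%.

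Recorded wounds of stage 2 or higher per randomized participant are 0.119 in control, 0.100 with prevention of mild wounds and 0.040 with better stage 1 detection. If only stage 2 detection improves (d2 = 0.95), they rise to 0.132.

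**Check 3: how often both outcomes look worse.** I drew 400,000 settings with random stage mix and detection, random improvement in detection, and risk ratios between 0.3 and 1. Recurrence looked worse in 18.7%, stage in 5.1%, at least one in 23.2% and both in 0.6%. With stage 1 detection improving alone, both never looked worse; with stage 2 detection alone, both did in 34%. These shares depend on the ranges drawn and are not probabilities for this trial.

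**Check 4: how few participants have a stage.** The wounded per arm number 26 × 0.25 = 6.5, 26 × 0.38 = 9.9 or 26 × 0.80 = 20.8 across the Background's incidence and recurrence figures. The stage difference detectable with 80% power is (1.96 + 0.84) × √(2/n), which gives 1.55, 1.26 and 0.87 SD.

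**The case against.** A reader might infer that a working intervention would look harmful on both outcomes at once. The documents and the arithmetic do not support that. Prevention makes recurrence look better, and better stage 1 detection makes stage look better. Each scenario misleads on one outcome only, and both together is a corner case.

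A reader might also infer that more stage 1 wounds are bound to be recorded under connected care. That is not established. The daily skin checks belong to mat use, which lasts about two weeks and ends before the 365-day window opens. Their findings go into a participant log, whereas outcomes come from medical records. The other check is a single confirmation on the visit day, and the article does not say that control visits lack one. A wound merely found earlier within the window leaves yes/no recurrence unchanged. Lasting changes in habit or care plan could still produce a difference, so the risk is possible but not certain.

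An analysis plan not shown might score wound-free participants as zero. That would remove the conditioning, but scenario B shows that such a score can still point the wrong way. The article itself states both the wound-dependent measure and the t test.

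On healing, the primary outcomes section is silent rather than contradictory, and an article condenses. Repeating the Aim 3 limit is a clarification. The same holds for the site of incident wounds, since the overall objective already speaks of seating-related injuries.

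Finally, this is a 52-person pilot looking for trends. That lowers the stakes of any single test, but not of an estimate carried into the full trial.

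**Conclusion.** The conditioning problem stands. As written, early identification is compared among participants selected after randomization by an event that the intervention aims to prevent. The bias can reverse the sign: 1.8 to 2.0 in mean stage while any wound falls from 50% to 35%, under assumed rates. The comparison would also rest on roughly 7 to 21 people per arm.

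The ascertainment problem with any-stage recurrence is conditional. It needs connected care to bring into the record wounds that would otherwise go unrecorded, and a large enough true reduction outweighs it. It does not make recurrence uninterpretable. The fair statement is that either outcome can mislead and that the two tend to move in opposite directions. This should be corrected before the analysis is fixed; it does not invalidate the trial.

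**What to change.** 1. Define early identification over all randomized participants, as the proportion with a new seating-area wound first recorded at stage 2 or higher within the 365-day window. Compare it as a proportion, with a confidence interval, in place of the t test on stage.
2. Report it beside any-stage recurrence in the same population, so that prevention and earlier detection can be read together.
3. Tabulate stage among wounded participants descriptively, without a between-group test.
4. In the primary outcomes section, restrict healing to wounds present at randomization, in line with the Aim 3 summary. This is a subgroup defined at baseline, not a randomization stratum, because the strata pool stage 1 with no wound.

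The cost is wording in the protocol and analysis plan; the abstracted data already include stage. The stage 2 or higher measure combines prevention with early detection and reduces but does not remove detection bias, as the rise from 0.119 to 0.132 shows, so both components should be shown. It will also be imprecise: for 25% against 30% with 26 per arm, the 95% half-width is 1.96 × √(0.25×0.75/26 + 0.30×0.70/26) = 0.24. The gain is a comparison that randomization protects, not power.
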